#### *12b. Analytic methods*

We will first conduct descriptive analyses to allow us to determine the characteristics of the sample we have enrolled. We will then analyze the specific outcomes as follows:

##### *Primary outcomes 1 and 2 and secondary outcomes 3, 4, and 5:*

For all primary and secondary clinical outcomes, the analytic approach will be the same. All analyses will be by intention-to-treat: subjects will be analyzed according to the intervention they were supposed to receive, whether or not they adhere to the defined intervention. This includes patients randomized to the intervention arm who are screened out of immediate ART initiation by the SLATE algorithm; they will remain in the intervention arm for data analysis. Primary analyses will be pooled across study countries, though we will also conduct stratified analyses by country to look for country-specific differences.

The analysis will begin with a simple comparison of the two treatment groups with respect to baseline predictors of outcomes to look for any imbalances. These potential confounders include demographic

(e.g. age, sex) and socioeconomic (education, distance from clinic, employment, etc.) variables, medications, baseline CD4 counts, and low BMI, among others.

We will then conduct a crude analysis comparing the proportion of patients achieving each dichotomous outcome by group and estimating crude risk ratios and crude risk differences and their corresponding 95% confidence intervals. This will be our primary analysis as we anticipate that randomization of over 1000 subjects should lead to balance in baseline covariates. Should any important imbalances occur by chance, we will proceed with an adjusted model as described below for the country-specific analyses.

Next, we will look for effect modification by important predictors of each outcome. The primary modifier will be country, as practices for care and treatment may differ across the different countries. We will also look for differences in effects stratified by age, sex, baseline BMI, CD4 count, and any other important demographic and clinical predictors of outcomes identified. Our analysis for effect modification will use a simple stratification of the primary analysis by the potential modifier and report crude risk differences and risk ratios and their corresponding 95% confidence intervals.

When stratified by these potential effect modifiers, because the sample sizes within groups will be smaller, it is possible that some baseline covariates may be imbalanced by treatment arm. To adjust for potential differences by baseline covariates, a log-linear regression model will be used to estimate adjusted risk ratios. Variables considered to be important in the univariate stage will be included in multivariate models. Adjusted analyses will include covariates which are unevenly distributed across treatment groups and which could plausibly affect retention or ART initiation. Each of these models can then be used to look for patient-level predictors of treatment uptake and retention in care.

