## **5. Study Design**

### *5a. Overview*

The study will be an individually randomized evaluation that will collect data from consented study subjects using questionnaires, a brief physical examination, a venous blood draw where not already done under routine care, and review of routine medical records. Patients randomized to the intervention arm will be initiated on ART if eligible under SLATE or referred for standard care if not eligible under SLATE. Health facility information that does not pertain to human subjects (e.g. unit costs) will also be collected. Figure 2 summarizes study design and procedures.

Figure 2. SLATE study procedures

[figure not shown]

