#### *6f. Randomization*

After the questionnaire has been completed, patients will be randomized to the intervention or standard groups of the study. Randomization envelopes will be generated in blocks of 6 and kept at the study sites. For each enrolled patient, the study assistant will open the next envelope in sequential order, read the randomization group, and record it on the case report form. The study assistant will then inform the patient of the randomization assignment.

Following randomization, standard group patients will be escorted to the clinic registration desk to resume their routine clinic visit. The study assistant will repeat the explanation of next steps in the study, which are limited to review of medical records by the study team, provide study payment as described below, and thank them for their willingness to participate in the study. The study team will have no further personal contact with patients in the standard group.

The study assistant will introduce intervention group patients to the study clinician for algorithm data collection. The study clinician will be a nurse, medical officer, or clinical officer at the same level as the individual responsible for ART initiation under standard care at the study site.

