### *7b. Blood draw*

Cryptococcal meningitis and other co-infections are more likely in patients with very low CD4 counts. Although new national guidelines in the study countries do not require the results of a CD4 count to establish treatment eligibility, most countries will continue to use CD4 counts to monitor patient condition. To avoid asking intervention group patients to wait in the clinic's queue for a blood draw, the study clinician will do a standard venous blood draw, following the same procedures that the clinic would otherwise use. Blood samples will be tested by the laboratories that serve the clinics, following routine procedures, and results will be placed in routine medical records so that the study clinics do not have to repeat the CD4 count for the same patients. The clinic may also use the blood sample for other baseline tests recommended in national guidelines, such as creatinine, hemoglobin, and for patients with CD4 counts under 100 cells/mm^3, cryptococcal antigen (CrAg). The clinic will follow routine procedures for laboratory tests; the study will only be responsible for drawing the required blood sample.

Study staff will monitor CD4 count results for all patients enrolled in the intervention arm. Under national guidelines in both countries, any patient who has a CD4 count under 100 cells/mm^3 and a positive cryptococcal antigen (CrAg) screening result should begin presumptive treatment for cryptococcal meningitis. Results of the CD4 count and CrAg screening test will only be available several days after study enrollment, however. To facilitate proper follow up of any intervention arm patient who does have a positive CrAg screening test, study staff will review CD4 count results for intervention arm patients as soon as the results are available at the study clinics. The study team will alert the clinic to any patient who has a CD4 count under 100 and request that the clinic trace the patient and provide follow up care as guidelines mandate.

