## **13. Human Subjects Considerations**

### *13a. Risks and protection against risks*

For this study, we will not collect any biomedical samples that would not be collected as part of routine care, nor will we implement any clinical procedures that are not routinely carried out under standard of care. The strategy being evaluated merely reorganizes data collection and accelerates the timing of events. The only non-routine data generated for the study itself will be responses to questionnaires. Study staff will conduct a brief physical exam and do a blood draw for intervention arm subjects, but both are procedures that are routinely performed and carry little risk. We therefore believe that our study poses no physical risks to subjects beyond those routinely encountered. It may, however, pose risks associated with loss to HIV care, emotional distress, and breach of confidentiality.

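### Section 12b relies on baseline CD4 count and BMI, but the protocol does not provide for capturing either one equivalently in the two arms

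*Protocol*

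**What the plan says.** Protocol section 12b gives CD4 and BMI three uses.

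- **Balance check.** The potential confounders to be compared between arms include "medications, baseline CD4 counts, and low BMI, among others".
- **Effect modification.** After country, the plan says: "We will also look for differences in effects stratified by age, sex, baseline BMI, CD4 count".
- **Adjustment.** The primary analysis is crude, but "Should any important imbalances occur by chance, we will proceed with an adjusted model". The selection rule is: "Adjusted analyses will include covariates which are unevenly distributed across treatment groups and which could plausibly affect retention or ART initiation".

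On collection, 6f places randomization after the questionnaire, and then: "The study team will have no further personal contact with patients in the standard group". Section 13a says: "Study staff will conduct a brief physical exam and do a blood draw for intervention arm subjects". Section 5a describes the draw, without naming an arm, as "a venous blood draw where not already done under routine care". Section 7b explains that the study draw spares intervention patients the clinic queue, and adds that "most countries will continue to use CD4 counts to monitor patient condition". Section 9d gives standard-arm patients only the questionnaire, identifier and completion sections of the case report form. Section 9e lists the most recent CD4 count as a record field for all subjects at the enrollment visit.

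**The concern.** A covariate used for a balance check, for strata or for adjustment should be available on the same terms in both arms. That holds most securely when it is collected before allocation. Here the study's own means of obtaining CD4, and perhaps BMI, operate after allocation and in one arm only.

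The CD4 value itself is not the difficulty, since assignment cannot change a CD4 count on the same day. The difficulty is whether a value exists. In the standard arm that may depend on the patient staying at the clinic long enough to be bled. Leaving care early is also how a patient fails both primary outcomes. If patients without a value are left out, the comparison is no longer between the groups as randomized.

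A second consequence concerns the adjustment rule. If CD4 is recorded for different kinds of patient in the two arms, the balance table may show a difference that reflects capture rather than chance. Section 12b makes observed imbalance the trigger for adjustment.

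**Working it through.** **Step 1. Sources by arm, as the protocol lists them.**

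| | Intervention arm | Standard arm |
|---|---|---|
| Weight, height, BMI in questionnaire topics (9d, section 1; 5 topics) | not named | not named |
| Weight, height, BMI in record fields (9e; 29 fields) | not named | not named |
| Study physical exam (9d section 4; 13a) | yes; its description does not name weight or height | not done |
| CD4 draw (5a, 7b, 13a) | study clinician, after randomization, unless already done | clinic, if and when it draws one |
| CD4 results followed by study staff (7b) | yes | no |
| CD4 abstracted from records (9e) | yes, most recent | yes, most recent |

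For BMI, no source usable for a between-arm comparison is listed. For CD4, the abstraction field is common to both arms, but what fills it can differ.

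**Step 2. Timing of CD4.** The enrollment field in 9e has no date or window, whereas the endpoint field asks for date and result. Patients may have been diagnosed earlier (5c), and results arrive some days after enrollment (7b). The value abstracted could therefore be old, same-day or later. The visit-level fields in 9e give visit dates and the numbers and types of tests. A later CD4 test can thus be tied to a visit, but results are not listed there.

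**Step 3. What selective missingness would do (illustration only).** The plan gives no figure on this point. Take the planning rates in section 11, 65% and 80%: difference 15.0 points, RR 0.80/0.65 = 1.23. Assume CD4 is known for all intervention patients and all standard-arm achievers. Let q be the assumed share of standard-arm non-achievers who have no CD4 and are excluded. The standard-arm proportion among patients with CD4 is then 0.65 / (0.65 + 0.35 × (1 − q)).

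| q | Standard arm appears as | Difference (points) | RR |
|---|---|---|---|
| 0 | 65.0% | 15.0 | 1.23 |
| 10% | 0.65/0.965 = 67.4% | 12.6 | 1.19 |
| 20% | 0.65/0.930 = 69.9% | 10.1 | 1.14 |
| 40% | 0.65/0.860 = 75.6% | 4.4 | 1.06 |

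If CD4 is missing equally often in standard-arm achievers and non-achievers, say 10% of each, the proportion is 0.585/(0.585 + 0.315) = 65.0% and nothing changes. The values of q are assumptions; nothing in the protocol points to one of them. The table describes all patients with a known CD4 taken together, not any one CD4 stratum.

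**Step 4. Which handling helps.** An adjusted log-link model was simulated under these assumptions: N = 400,000, true RR 1.23, 40% with low CD4, outcome RR 0.85 for low CD4, and CD4 missing only in the standard arm. Missingness was set at 10% or 30% of standard-arm never-initiators. Never-initiators were taken as 76% of non-achievers, from the earlier trial's RR of 1.36 with its intervention arm set at 100%: (1 − 1/1.36)/0.35 = 0.76. Complete cases gave RR 1.20 and 1.13 to 1.14. A missing-value indicator gave the same. Multiple imputation with arm and outcome in the imputation model gave 1.23 in both.

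**The case against.** The strongest reply is that the study draw replaces a routine one. Section 7b uses the same procedures and laboratories, and the result is filed so that the clinic need not repeat it. Section 13a says that no samples are taken beyond routine care. Standard patients resume their clinic visit the same day, and 9e abstracts CD4 for all subjects at that visit. Most standard patients may therefore have a comparable value, and the protocol does not say how many would not. This stands, and it rules out reading the plan as having no CD4 in the standard arm.

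It can also be said that the exact baseline window and the handling of missing data belong in a statistical analysis plan, and that 12b nowhere commits to complete cases. That stands too: a reader might infer that 12b prescribes a biased analysis, and it does not. What an analysis plan cannot do is create measurements that were not taken alike in both arms.

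The case report form is not shown and might contain weight and height. If they sit in the exam section, however, 9d leaves that section blank for the standard arm.

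Finally, 12b speaks of imbalance arising by chance, so an artefact of capture does not strictly require adjustment. That is fair, but a balance table does not show which kind of imbalance it displays.

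**Conclusion.** The point holds as a minor one. Section 12b assigns baseline CD4 and BMI roles that need equivalent capture, and the protocol does not provide for it. BMI has no listed source common to both arms. CD4 has a common field, but no date or window, and a study-ensured draw in one arm only.

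A reader might go further and conclude that the trial's main result is at risk. The documents do not support that: the primary analysis is crude and pooled and uses neither variable. Nor do they support any particular size of bias. The figures in the working rest on assumed missingness, and they apply only if patients without CD4 are excluded and missingness relates to outcome. If it does not, there is no bias. Under the illustrated pattern, with standard-arm non-achievers lacking CD4, the direction is toward no effect.

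What is exposed is limited to the balance table, the CD4 and BMI strata, and any model adjusted for either variable.

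**What to change.** 1. **BMI.** Record weight and height in section 1 of the case report form, in both arms, before the envelope is opened. Section 11 refers to early enrollment, so some patients are already past that point. For them, abstract routine enrollment-visit values in both arms. If neither is feasible, remove BMI from 12b.
2. **CD4.** Add the date to the enrollment field in 9e. Define baseline by one rule for both arms: the latest value up to a short fixed window after enrollment (for example 7 days) and not after ART start. Report availability by arm, because a short window may itself leave more standard-arm patients without a value.
3. **Adjustment trigger.** Limit imbalance-triggered adjustment to variables collected before randomization in both arms.
4. **CD4 analyses.** Label CD4-stratified results exploratory. If CD4 is used, do not rely on complete cases alone; use multiple imputation with arm and outcome in the imputation model. A separate missing-CD4 stratum is not a remedy, because the strata with known CD4 would stay biased.

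The cost is a few minutes per patient, one date field and some wording in 12b. The downside is that CD4 analyses carry less weight and CD4 can no longer trigger adjustment.

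### The primary crude pooled comparison ignores the sites within which allocation is balanced, and covariates for the added adjusted model are chosen after seeing the data: a modest, free gain in precision and clarity

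*Protocol*

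**What the plan says.** Section 5b names three clinics in each of two countries. On allocation, section 6f says: "Randomization envelopes will be generated in blocks of 6 and kept at the study sites". The study assistant opens the next envelope in sequence for each enrolled patient.

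Section 12b gives one approach for both primary outcomes and for secondary outcomes 3 to 5. It states "Primary analyses will be pooled across study countries", with further analyses by country. The comparison consists of "estimating crude risk ratios and crude risk differences and their corresponding 95% confidence intervals", and its status is explicit: "This will be our primary analysis as we anticipate that randomization of over 1000 subjects should lead to balance in baseline covariates". Country enters only as an effect modifier, through stratification. Site is not among the covariates or modifiers named for these outcomes.

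The next sentence adds a conditional step: "Should any important imbalances occur by chance, we will proceed with an adjusted model as described below for the country-specific analyses". The model described there is log-linear. Two rules choose its covariates: "Variables considered to be important in the univariate stage will be included in multivariate models" and "Adjusted analyses will include covariates which are unevenly distributed across treatment groups". The second rule also requires that the covariate could plausibly affect initiation or retention.

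**The concern.** There are two separate issues.

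**Precision.** When blocks are filled within sites, the two arms have nearly the same site mix. Differences between sites then hardly contribute to the chance variation of the treatment comparison. The crude standard error still counts them as noise, so it is too large whenever site rates differ. The protocol gives reason to expect differences. Section 5c says that implementation of treat-all may vary by site, section 12b says that practices may differ by country, and section 11 expects the proportion screening in at the South African sites to range from 32% to 67%. The stated justification, balance from a large sample, concerns confounding and does not touch this.

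**Choice of adjusted model.** Whether an adjusted analysis is run, and with which covariates, depends partly on the observed imbalance and on univariate results. After randomisation, imbalance is a poor guide to which covariates matter; prognostic strength is the better one. Some covariates named in section 12b may also be measured differently by arm. Under sections 7b and 9d the physical examination and study blood draw follow randomisation and are done in the intervention arm only, while section 9e takes the CD4 count from routine records. An apparent imbalance in CD4 count or BMI could therefore reflect how it was recorded.

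**Working it through.** **1. The plan's own figure (section 11).** Inputs: 65% versus 80%, alpha 0.05 (taken as two-sided), power 90%, 1:1 allocation.

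- Uncorrected: n = [1.96·√(2·0.725·0.275) + 1.2816·√(0.65·0.35 + 0.80·0.20)]² / 0.15² = 184.1, so 185 per group.
- With continuity correction: (184.1/4)·[1 + √(1 + 4/(184.1·0.15))]² = 197.2, against the stated 197.

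The planning rates and two-sided alpha are therefore read correctly.

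**2. Crude versus site-stratified interval for the risk difference.**

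- From section 11: a maximum of 480 in Kenya and 660 in South Africa, so 1140 in all and 570 per arm.
- Assumed: equal sites within country (80 per arm at each Kenyan site, 110 at each South African site), and the same between-site standard deviation s in both arms. The protocol gives no site rates for either primary outcome, so s is varied.
- Crude variance: (0.65·0.35 + 0.80·0.20)/570 = 0.3875/570. The 95% half-width is 1.96·√(0.3875/570) = 5.11 points.
- Stratified variance: the mean within-site binomial variance is p(1−p) − s² in each arm, which gives (0.3875 − 2s²)/570.
- Actual coverage of the crude interval: 2Φ(1.96·r) − 1, where r is the ratio of crude to stratified standard error.

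| s (points) | 0.3875 − 2s² | Stratified half-width (points) | Crude too wide by | Crude coverage |
|---|---|---|---|---|
| 0 | 0.3875 | 5.11 | 0% | 95.0% |
| 5 | 0.3825 | 5.08 | 0.7% | 95.15% |
| 10 | 0.3675 | 4.98 | 2.7% | 95.6% |
| 13 | 0.3537 | 4.88 | 4.7% | 96.0% |
| 15 | 0.3425 | 4.80 | 6.4% | 96.3% |

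At s = 15 the assumed site rates push one intervention-arm rate just past 100%. Capping it at 99.5% gives 4.81 points and 6.3%. The ratio r does not depend on sample size, so the percentages also hold for the roughly 960 patients in the protocol summary.

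**3. Power.** Power of the crude test is Φ[(d − 1.96·SE crude)/SE stratified]. For the stratified test, SE stratified is used in both places.

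- At the planned d = 0.15, both exceed 99.9% for every s in the table.
- For a smaller effect, 65% versus 73% (assumed, not in the protocol), with s = 10 points: the crude variance sum is 0.2275 + 0.1971 = 0.4246 and the stratified sum is 0.4046. Power is 84.0% crude and 85.1% stratified.

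**4. How often the trigger might fire.** The protocol gives no threshold. If an important imbalance meant p < 0.05 (assumed) on k independent variables, the chance of at least one is 1 − 0.95^k. That is 23% for k = 5, 34% for 8, 40% for 10 and 46% for 12.

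**5. Does the trigger damage the test?** Simulation with 1140 patients, site standard deviation 10 points and eight modestly prognostic covariates (all but the total assumed). There were 5000 runs under the null (Monte Carlo standard error about 0.3 points) and 3000 for power (about 0.7 points).

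| Analysis | Null rejection | Power, 8-point effect |
|---|---|---|
| Crude | 4.6% | 82.8% |
| Imbalance-triggered | 4.5% | 83.1% |
| Either of these two significant | 5.0% | 83.9% |
| Fixed adjustment for site and all covariates | 5.6% | 86.4% |

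The triggered rule does not raise the error rate, and it recovers almost none of the power that fixed adjustment gives. The 5.6% lies within two Monte Carlo standard errors of 5%.

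**The case against.** The strongest defence is that nothing in the plan yields a wrong inference. A crude risk ratio and difference are valid under randomisation, any error in the interval is on the cautious side, and power at the planned effect is not at risk. All of that stands.

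Two stronger readings are tempting.

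- **That the plan leaves open which estimate is primary.** The text does not support this. It names the crude result as primary and presents the adjusted model as a further step. It does not say that the adjusted result would replace the crude one, although a sentence saying it will not would help.
- **That covariates enter solely because they look unbalanced.** This is not so either. Univariate importance is a second route in, and the imbalance rule carries a plausibility condition, so prognostic relevance is already part of the rule.

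It is also fair to object that stratification by site is an inference. The protocol does not use the word in section 6f, and the inference rests on blocked envelopes being held at the sites and opened in order. The screening-in range of 32% to 67% is not a range for a primary outcome, because patients who screen out are referred to start ART under standard care and can still meet the 28-day endpoint.

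Finally, a threshold and covariate list could properly sit in a statistical analysis plan. Their absence is not the point. The protocol itself fixes an unstratified primary analysis and a data-led rule for adjustment, and both can be improved.

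**Conclusion.** The point holds as a minor to moderate, cost-free improvement. The primary analysis omits a factor on which allocation is in effect balanced, and the reason given does not address the consequence. The crude interval is about 1% to 6% too wide if between-site standard deviations are 5 to 15 points, and exactly right if sites do not differ. These sizes rest on assumed site spreads, equal site sizes within country and a common spread in both arms.

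A reader might infer a serious loss of power or a distorted error rate. The figures show neither: power for 65% versus 80% is above 99.9% with or without stratification, and the imbalance trigger left the null rejection rate at about 5% or below. What is left on the second issue is that the supportive adjusted result would rest on a model chosen partly from the data, possibly with covariates recorded differently by arm.

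**What to change.** In section 12b:

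- Make the site-stratified risk difference and risk ratio (for example Mantel-Haenszel), each with a 95% confidence interval, the primary analysis, and report the crude figures as supportive. With near 1:1 allocation within sites the point estimates should hardly move; the gain is in the interval.
- Delete the imbalance trigger and the univariate screen. Put in their place one prespecified adjusted analysis with site and a short list of prognostic variables collected before randomisation in both arms, such as age, sex and time of diagnosis from the questionnaire. State that it is supportive.
- Optionally, report the difference between the two countries' risk differences with its confidence interval, since country is named as the main effect modifier.
- State in section 6f that allocation is stratified by site, if that is how the envelopes are generated.

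The cost is about one paragraph of analysis wording. No new data and no change in sample size are needed.
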